#### Implementation

Participants will be recruited in blocks of 32 clusters linked by m2m. Households will be randomly selected from the assigned communities, and recruitment will proceed until 60 households are recruited in each block of 32 clusters.

### Assignment of Interventions: Blinding

#### Who Will Be Blinded

Due to the nature of the intervention, CHAMP facilitators, research assistants, and participants will be aware of condition allocation (based on cluster assignment). The range of conditions and allocation status of other enrolled clusters will be concealed from participants to reduce the risk of contamination. Trial statisticians conducting analyses on postintervention effects will be blinded to the assignment condition of clusters.

#### Procedure for Unblinding if Needed

This is not applicable for this study.

### Data Collection and Management

#### Plans for Assessment and Collection of Outcomes

This study will include quantitative and qualitative procedures for data collection. Data collected will consist of pretest-posttest parent and adolescent behavior questionnaires, parent cultural determinants of engagement, digitally tracked engagement data, and facilitator process data. All data will be collected using paper-and-pen forms. Individual semistructured interviews will be conducted to further explore participants’ engagement with ParentText and observed behavior outcomes.

#### Quantitative Data Collection

##### Baseline and Postintervention Surveys

Parent and adolescent behavior outcome surveys will be administered at baseline and the postintervention time point. Data collection will occur at the household level or at a meeting venue at the designated DREAMS schools. Data collectors will be 32 CHAMP implementers fluent in written English, isiZulu, or siSwati trained in ParentText delivery and study procedures such as interview techniques, research ethics, safety protocol, data management and security, informed consent, and adverse event report procedures. CWBSA and local researchers will conduct training and supervision of data collection. All measures, interview guides, workshop modules, and ParentText content will be translated from English into isiZulu and siSwati. Considering potential low literacy levels among some participants, data collection staff will read out the survey questions and response options, and participants will follow along. Facilitators will capture all data collected via Open Data Kit–based surveys (Get ODK Inc).

##### Cultural Determinants of Engagement Surveys

Cultural determinant outcome surveys will be collected at the ParentText onboarding session.

##### Chatbot Engagement Data

ParentText engagement data will be tracked digitally by the software developers, IDEMS International.

##### Engagement on Human Support Components

Facilitators will record in-person attendance and WhatsApp group discussion participation of parents enrolled in the cluster to which they were assigned.

##### Cost Data

Financial and economic costs associated with the resource inputs required to deliver the intervention and the intervention components will be considered in this study. Financial costs are defined as actual expenditures incurred on resource inputs, and economic costs are defined as the market value of all donated and subsidized resource inputs. Intervention costs include facilitator costs such as those associated with their training to deliver ParentText (captured as their time spent attending training sessions) and with preparing and delivering specific intervention components. Physical space used to deliver in-person sessions, as well as expenditures related to travel and supplies (such as internet data and cell phones), will be audited and valued. Local researchers and coordinators will collect resource use data *in*
*real time* (ie*,* alongside the full study trial) via the completion of weekly Open Data Kit–based surveys. Costs related to the development of ParentText and content adaptation and translation will be included as a capital start-up cost. Because the cost analyses will be conducted from the provider perspective, costs incurred by participants (travel expenditure and opportunity costs) will be excluded. While the implementing organization’s program monitoring and evaluation costs will be included in cost estimates, broader research activity costs will be excluded.

#### Qualitative Data Collection

A subsample of parents will be purposively selected and invited via phone for in-person or over-the-phone individual semistructured interviews. Purposive selection will be based on gender and those with low, medium, and high levels of engagement (approximately 5 male and 5 female parents from different age groups). Engagement levels will be operationalized based on quartiles (ie, low engagement=lowest quartile; medium engagement=second and third quartile; high engagement=highest quartile). The subsample size will depend on the heterogeneity and availability of participants. To ensure that the interviews are standardized, interviewers will follow an interview guide developed by the research team. The interviews will be conducted by a trained qualitative researcher with the support of an interpreter. In addition, focus group discussions will be conducted with the implementing partner, m2m, to understand the challenges and opportunities during implementation.

#### Plans to Promote Participant Retention and Complete Follow-Up

To promote retention in the chatbot, participants will receive badges for each module completed, a trophy for each goal, and a certificate of completion at the end of the program. Participants attending the in-person sessions will be provided with refreshments at each session and receive a certificate of acknowledgment at the end of the fourth session.

### Data Management

This study will implement the following data management measures to ensure confidentiality, security, and safety. Per the US Agency for International Development implementation guidance, raw baseline and postintervention data collected will be captured to the Community-Based Intervention Monitoring System database, a South African community-based intervention monitoring system. Zoë-Life, a global training and consulting firm, will assist m2m with the deidentification of the data before they are transferred to the University of Oxford central server via an application programming interface. A Community-Based Intervention Monitoring System or system-generated ID will be assigned to uniquely identify each participant. ParentText engagement data will be automatically stored through end-to-end encryption to an IDEMS International server. During the data merging process, participants will be assigned a unique study code. The data on the University of Oxford central server will be managed by the University of Oxford Global Parenting Initiative data management team with technical support from the University of Oxford Department of Social Policy and Intervention IT team. Hard copies (eg, paper-and-pen questionnaires and participant attendance records of WhatsApp group and in-person sessions) will be stored in locked fireproof storage spaces and be permanently destroyed after being uploaded to a secure web-based data repository managed by the University of Oxford. Consent forms will be retained for at least 3 years after the study is published in compliance with the funders’ requirements.

### Confidentiality

Anonymized baseline and postintervention data sets will be stored in a password-protected server at the University of Oxford. Access will be controlled and only granted to members of the study team or partnered institutions that aided in the research project. Audio recordings of interviews and focus group discussions will be transcribed verbatim and stored in password-protected devices and will then be securely uploaded and backed up at the University of Oxford server. Once uploaded to the server, audio files will be deleted from the recording devices. After anonymizing and verifying the transcripts, audio recordings will be permanently deleted from data repositories. All Excel and Word (Microsoft Corp) files will be named following a standardized protocol, including the download date, to ease version control. Deidentified interview transcripts and data sets will only be shared by the Global Parenting Initiative data manager by granting access to specific files through the OneDrive for Business at the University of Oxford. Deidentified data sets will be stored securely for perpetuity and use per UK Data Archive guidance [90]. Raw baseline and postintervention data collected will be owned by the m2m South Africa office. Participants’ data will be stored by m2m in compliance with the South African Protection of Personal Information Act. IDEMS International will own the raw data collected through ParentText.

### Plans for Collection, Laboratory Evaluation, and Storage of Biological Specimens for Genetic or Molecular Analysis in This Trial or Future Use

This is not applicable for this study as no biological specimens for genetic or molecular analysis will be collected.

### Data Analysis

#### Statistical Methods for Primary and Secondary Outcomes

This study will examine the main effects of each component level on user engagement and behavior outcomes**.**

##### Engagement Outcomes

Baseline differences between groups will be described using proportions, means, and SDs. The main effect of each intervention component and interaction effects between components on primary and secondary engagement outcomes will be estimated using multilevel models (including mixed models if outcomes are continuous, Poisson models if outcomes are counts or count distributed, and logistic models if outcomes are binary). Separate models will be tested using effect coding [91,92]. Each model will specify 3 levels to account for the longitudinal and clustered nature of the data—repeated measures are nested within individuals, which are, in turn, nested within clusters. Level 1 will include a term for categorical time (pre- and posttest time points) and for the interaction between time and intervention status, level 2 will include terms for individual sociodemographics such as age (parent and adolescent) and gender (parent) and other individual-level covariates centered at the sample mean, and level 3 will include terms for the intervention components and the stratifying factor. Robust SEs will also be estimated to adjust for clustering. This study will report the direction and magnitude of β, incidence risk ratios, and odds ratios at a significance level of *P*<.10 with 90% CIs. Two-tailed tests will be conducted across all analyses.

##### Behavioral, Mental Health, and Educational Outcomes

The main effect of each intervention component and interaction effects between components on behavioral, mental health, and educational secondary outcomes will be estimated using the same multilevel models and specifying the same levels and structures as with the engagement outcomes. Within-group analyses will also be conducted to examine pretest-posttest differences across the sample accounting for clustering in analyses.

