The study will randomly assign 32 clusters split equally (n=8 clusters) across the 4 different treatment conditions. A total of 1920 parents and their adolescent girls aged 10 to 17 years (approximately 60 parents and 60 adolescent girls per cluster) will be recruited to participate in the study. Each cluster will be randomly assigned a dedicated community-based facilitator to deliver the in-person and WhatsApp support group sessions. The study will adopt a between-cluster assignment to prevent contamination across experimental conditions.

**Table 1 table1:** Experimental conditions for a 2 × 2 factorial trial (n=32 clusters, n=60 parent-adolescent dyads, and N=3840 participants).

Condition	Clusters^a^ (n=32), n (%)	ParentText (always on)^b^	In person (1 session vs 4 sessions)^c^	WhatsApp groups (yes vs no)^d^
1	8 (25)	On	1	No
2	8 (25)	On	1	Yes
3	8 (25)	On	4	No
4	8 (25)	On	4	Yes

^a^*Cluster* refers to parent and adolescent groups linked to a designated facilitator.

^b^*Always on* refers to the provision of the chatbot without any external support.

^c^Parents and adolescent girls will receive either 1 or 4 in-person sessions.

^d^Parents will either receive (yes) or not receive (no) facilitated WhatsApp groups.

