##### Adult and Child Behavior Outcomes

Data collection of parent- and adolescent-reported mental health and behavior outcomes will occur at 2 time points: baseline and postintervention. Outcome measurements will be standardized to capture the occurrence of practices and behaviors over the “past month (last 30 days).”

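### The pre/post model for behavioural outcomes names no cluster-by-time variance, and the article does not say that the reported tests rest on the robust standard errors it adds

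*Protocol article*

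**What the plan says.** The Engagement Outcomes section under Data Analysis sets out the multilevel model: "repeated measures are nested within individuals, which are, in turn, nested within clusters". It places terms by level: "Level 1 will include a term for categorical time (pre- and posttest time points) and for the interaction between time and intervention status"; individual covariates at level 2; and "level 3 will include terms for the intervention components and the stratifying factor". The level 3 list holds fixed terms only. No random slope for time or cluster-by-time variance is named, and none is excluded. The section then adds: "Robust SEs will also be estimated to adjust for clustering". Results are to be reported at P<.10 with 90% CIs.

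The next section carries this model unchanged to the behavioural, mental health and educational outcomes, whose component effects are to be estimated "using the same multilevel models and specifying the same levels and structures as with the engagement outcomes". Data collection for those outcomes "will occur at 2 time points: baseline and postintervention".

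On the clusters, the Trial Design overview says: "The study will randomly assign 32 clusters split equally (n=8 clusters) across the 4 different treatment conditions". The footnote to Table 1 says that a cluster "refers to parent and adolescent groups linked to a designated facilitator". One facilitator therefore serves each cluster, and each component main effect compares 16 clusters with 16.

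**The concern.** With two time points, the component effect on a behavioural outcome is the time-by-component term, which is a contrast of pre-to-post change. A random intercept for the individual and one for the cluster are each shared by both occasions, so both cancel from the change. The model-based standard error is then built from individual residual variation alone, although whole facilitator groups were randomised.

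If some facilitators produce more change than others, for instance because sessions are delivered better, change is correlated within clusters and that standard error is too small. The Secondary Hypotheses expect the most intensive package to do best on these outcomes. There are many of them, several with both parent and adolescent report, and each is tested at the 10% level. Understated standard errors would add false claims of benefit.

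**Working it through.** **The plan's own figure.** The Sample Size section gives minimum detectable differences of 0.168 to 0.298 (80% power) and 0.197 to 0.351 (90% power) for ICC 0.02 to 0.10. With 16 v 16 clusters of 60, SD 1 and two-sided 10%:

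MDES = (1.645 + z_power) × √{4[ICC + (1 − ICC)/60]/32}

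- 80% power: 2.4865 × √(4 × 0.03633/32) = 0.1676, and 2.4865 × √(4 × 0.1150/32) = 0.2981.
- 90% power: 0.1972 and 0.3509 by the same formula.

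The stated figures reproduce. The power calculation therefore counts between-cluster variance in full, whereas the model-based standard error of the time-by-component term does not.

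**Inputs for the check**
- 32 clusters, 8 per condition; nominal level 10%, two-sided (Trial Design overview, Sample Size).
- Planned cluster size 60. Achieved size from the abstract: 744/32 = 23.25 caregivers onboarded and 1009/32 = 31.5 participants enrolled, so about 23 to 31.
- Assumption: ICC of the change score, ρ, from 0.01 to 0.05. The documents give no value; the planning ICCs of 0.02 to 0.10 concern outcome level.

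To link the two: if the cluster autocorrelation is c and the individual autocorrelation is r, then ρ = ICC(1 − c)/[ICC(1 − c) + (1 − ICC)(1 − r)]. With c = 0.8 and r = 0.5 (both assumed), the planning ICCs of 0.02, 0.05 and 0.10 give ρ = 0.008, 0.021 and 0.043. With c = 1, ρ = 0.

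**Model-based standard error.** The true standard error exceeds the model's by √DE, where DE = 1 + (m − 1)ρ. Type I error is 2[1 − Φ(1.645/√DE)].

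| Per cluster | ρ | DE | √DE | Type I error |
|---|---|---|---|---|
| any | 0 | 1.00 | 1.000 | 10.0% |
| 23 | 0.01 | 1.22 | 1.105 | 13.6% |
| 23 | 0.05 | 2.10 | 1.449 | 25.6% |
| 31 | 0.01 | 1.30 | 1.140 | 14.9% |
| 31 | 0.05 | 2.50 | 1.581 | 29.8% |
| 60 (planned) | 0.01 | 1.59 | 1.261 | 19.2% |
| 60 (planned) | 0.05 | 3.95 | 1.987 | 40.8% |

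**Cluster-robust standard error, uncorrected, normal reference.** The cluster-level model has five fixed terms (intercept, two components, interaction, district), leaving 32 − 5 = 27 df. In a balanced layout the uncorrected sandwich divides the cluster residual sum of squares by 32 instead of 27. The effective critical value is 1.645 × √(27/32) = 1.511, and P(|t27| > 1.511) = 14.2%, whatever ρ is. Without the district term (28 df) it is 1.645 × √(28/32) = 1.539, giving 13.5%.

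**Corrected.** A small-sample-corrected sandwich, or a cluster-level test, referred to t with 27 df (critical value 1.703) holds the level.

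**Simulation.** In 40,000 null trials per setting, with change scores, effect coding and a district term, model-based error was 13.7% to 29.6% at 23 and 31 per cluster for ρ = 0.01 to 0.05. Uncorrected robust error was 13.8% to 14.6%. Corrected error was 9.7% to 10.3%.

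**Precision from baseline adjustment.** For individual-level variation with equal variances and pre-post correlation r, the posttest adjusted for baseline has variance 1 − r², and the change score has 2(1 − r). The ratio is (1 + r)/2, which is 0.85 at r = 0.7 and 0.65 at r = 0.3. The saving is therefore 15% to 35% (r assumed).

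**The case against.** The strongest reply is the robust standard error sentence. Standard errors clustered on the 32 facilitator groups take in variation in change even when the random part omits it, and the behavioural section inherits that provision. A reader might infer that the plan ignores facilitator effects on change, or that the higher error rates describe the planned analysis. The documents do not support that. The sentence shrinks the problem to about 14% v 10%, and to nothing if a small-sample correction is used. What stands is that the robust standard errors are announced as an addition. The text does not say that the reported P values and CIs come from them.

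Second, random-effect detail and degrees of freedom are commonly left to an analysis plan, and the text does not exclude a random slope. Fair, and silence on those alone would be no finding. But the article does fix the levels, the terms at each level and the time interaction, and carries that structure over to these outcomes. The point is about that stated choice.

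Third, the size under model-based standard errors rests on an assumed ρ. Also fair. It is not certain that change clusters. The CHAMP implementers collect the data at both time points, so a stable interviewer effect would largely cancel. The figures at 60 per cluster do not apply to the achieved sample.

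Fourth, a reader might infer that the wrong package could be selected. The section on selecting the package screens components on the primary engagement outcome, so behavioural P values do not drive that step.

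**Conclusion.** The point holds in limited form, for secondary outcomes with two time points. As written, the model-based standard error of the time-by-component term leaves out between-facilitator variation in change, and the text does not say which standard errors support the reported inference. At nominal 10%:

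- about 14% with uncorrected cluster-robust standard errors and 32 clusters, with no assumption about ρ needed;
- about 14% to 30% with model-based standard errors at 23 to 31 per cluster, if ρ is 0.01 to 0.05, and 10% if ρ is zero;
- about 10% with small-sample-corrected cluster-level inference.

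The calculation assumes a continuous outcome, equal cluster sizes and complete pairs. It was not repeated for the Poisson and logistic models that the plan also allows. Modelling change is an accepted approach; the precision it gives up is a reason to prefer the first fix, not an error in the plan.

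**What to change.** For the two-time-point outcomes, analyse the posttest value adjusted for the participant's own baseline value. Include the two component effects, their interaction, district and a cluster random intercept. Use small-sample degrees of freedom: 32 − 5 = 27, or 26 if the cluster-mean baseline is added as a further cluster-level covariate.

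Alternatively, keep the three-level model, add a cluster-by-time random effect, and state that P values and 90% CIs rest on small-sample-corrected standard errors.

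The cost is a change of analysis wording; the baseline measures are already planned. CIs will be wider than the understated model-based ones, partly offset under the first option by the precision gained from baseline adjustment.

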#### Analysis of Qualitative Data

Qualitative data will be analyzed using NVivo (QSR International) and Word through framework analysis [93]. Qualitative data analysis will be performed simultaneously with quantitative analysis to assess whether qualitative themes generalize to the entire population and expand the understanding of quantitative results. The analysis will include 5 stages: familiarization, identification of themes, indexing, charting and summarization, and interpretation and mapping. Researchers will begin by familiarizing themselves with the transcripts and identifying emerging themes. A code will then be assigned to each theme and subtheme at the indexing stage. After themes are indexed, they will be charted and summarized. Finally, interpretation and mapping will be used to understand the findings more deeply.

#### Cost-Effectiveness Analysis

This study will evaluate the efficiency and affordability that results from the expansion or contraction of the ParentText delivery package from the provider’s perspective. Program implementation costs and outcome data will be recorded and analyzed in Excel. The total costs of the intervention (setup and operating costs) for each intervention component and the average cost per participant enrolled (unit cost) will be estimated. The trial’s primary outcome relates to levels of user engagement (ie, the overall number of modules completed by participants), and this will be used to understand the cost-effectiveness of the intervention components that will maximize user engagement with ParentText. The estimated cost-to-engagement ratio for each of the intervention components will be calculated and compared to assess the incremental cost-effectiveness of each component. All costs will be adjusted to 2023 US dollars using the Consumer Price Index.

#### Analytical Strategy for Selecting the Most Optimal Intervention Package

We will use the decision-making framework presented by Collins [52] to select the most effective, cost-effective, and feasible components and component levels for inclusion in the optimized intervention before testing in a randomized controlled trial. As shown in Figure 3, the most optimal intervention package will be the one presenting higher effectiveness while considering resource and feasibility constraints. First, the main effects of each component on primary engagement outcomes will be identified and averaged across the other intervention components. Second, intervention components will be divided into a screened-in and screened-out set based on their positive effectiveness on participants’ engagement with ParentText. Intervention components with negative or no effect will be included in the screened-out set, and the lower level of that component will not be considered further. Third, intervention components in the screened-in set (ie, those showing positive effects and cost-effectiveness) will be considered for further evaluation. Results from qualitative interviews and focus group discussions conducted with the implementing partner will be used to further understand the feasibility, acceptability, effectiveness, and cost-effectiveness of the retained component levels and draw conclusions to develop the final optimized ParentText delivery package.

The posterior expected value approach will be included in the decision-making process to increase the robustness of our results. In previous research, the posterior expected value approach has modestly outperformed the component screening approach in accuracy, sensitivity, and specificity [94]. Estimates of the posterior expected value for each intervention component will be obtained using Markov chain Monte Carlo methods. We will prefer intervention components with higher Markov chain Monte Carlo posterior distribution of mean outcomes.

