### Trial Design

#### Overview

This study design was derived from the multiphase optimization strategy framework developed by Collins [52], which consists of 3 stages: preparation, optimization, and evaluation. In the multiphase optimization strategy, intervention optimization is the process of evaluating and identifying from a set of intervention components the combination with the most effective and scalable design that can be obtained subject to existing constraints such as limited financial and human resources [49]. The preparation phase of this study took place between October 2022 and February 2023. It comprised a formative evaluation with stakeholders from government and nongovernmental organizations (NGOs) in South Africa. The findings of this phase informed the selection of the intervention components for inclusion in this trial.

The ParentText Optimisation Trial will be conducted from August 21, 2023, to November 10, 2023, in Mpumalanga, South Africa. It will use a 2 × 2 cluster-randomized experimental design to investigate the effectiveness and cost-effectiveness of two components delivered externally from the ParentText chatbot: (1) in-person sessions with parents and adolescent girls (1 or 4 sessions) and (2) facilitated WhatsApp support groups with parents (yes or no). All caregivers and adolescent girls will be onboarded to ParentText in the in-person session (the first session for those assigned to receive 4 in-person sessions). The 2 × 2 factorial trial will include four experimental conditions (Table 1):

Condition 1: ParentText chatbot and 1 in-person session (onboarding to ParentText) with parents and adolescent girlsCondition 2: ParentText chatbot, 1 in-person session (onboarding to ParentText) with parents and adolescent girls, and facilitated WhatsApp groups for parentsCondition 3: ParentText chatbot and 4 in-person sessions (with the first session focused on onboarding to ParentText) with parents and adolescent girlsCondition 4: ParentText chatbot, 4 in-person sessions (with the first session focused on onboarding to ParentText) with parents and adolescent girls, and facilitated WhatsApp groups for parents

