#### Primary Hypotheses

The primary hypotheses are as follows:

Facilitated WhatsApp support groups (yes or no): we hypothesize that parents receiving the ParentText delivery package combined with web-based support via WhatsApp groups will have higher engagement rates than those receiving the ParentText delivery package without facilitated support via WhatsApp groups.In-person sessions (1 or 4 sessions): we hypothesize that parents receiving the ParentText delivery package combined with 4 in-person sessions will have higher engagement rates than those receiving the ParentText delivery package with 1 in-person session.Incremental cost-effectiveness: we hypothesize that, while the inclusion of facilitated WhatsApp groups will be more cost-effective than not including facilitated WhatsApp groups based on the incremental cost advantage, the higher dosage of in-person sessions will not be a cost-effective component.

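### The component-screening sentence is reversed as written: a component without benefit is screened out, yet it is its lower level that is dropped

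*Protocol article*

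**What the plan says.** The Protocol article sets out the selection in three steps (Analytical Strategy for Selecting the Most Optimal Intervention Package).

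1. For the primary engagement outcome, "the main effects of each component on primary engagement outcomes will be identified and averaged across the other intervention components".
2. Components are "divided into a screened-in and screened-out set based on their positive effectiveness on participants’ engagement with ParentText". A component whose effect is negative or absent "will be included in the screened-out set, and the lower level of that component will not be considered further".
3. Then "intervention components in the screened-in set (ie, those showing positive effects and cost-effectiveness) will be considered for further evaluation".

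The section opens by defining the best package as the more effective one, given limits on resources and feasibility. It adds that interviews, focus groups and a posterior expected value approach will inform the decision, and it refers to Figure 3 for the strategy. Trial Design (Overview) and Table 1 give each component two levels: 1 or 4 in-person sessions, and WhatsApp groups absent or present.

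**The concern.** With two levels per component, dropping one leaves the other. For a component that shows no benefit, step 2 drops the lower level: a single session, or no WhatsApp group. What remains is the higher and more resource-intensive level, for which no benefit was seen. One would expect screening out to do the opposite.

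Choosing the package for the next randomized trial is a stated objective of this one (Secondary Objectives, last item). A team that applies step 2 as worded could carry a costlier level forward because it failed. A team that applies the evident intent would be departing from the published text. The protocol should not leave that to be settled after the results are known.

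**Working it through.** **Inputs.** The levels and condition numbers come from Table 1: condition 1 = 1 session, no WhatsApp; 2 = 1 session, WhatsApp; 3 = 4 sessions, no WhatsApp; 4 = 4 sessions, WhatsApp. The three steps are those of the selection section.

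**The step 2 clause applied to Table 1.** The clause acts only on screened-out components.

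| Screened out | Conditions struck by the clause as worded | Conditions struck with *higher* in place of *lower* |
|---|---|---|
| WhatsApp only | 1 and 3 | 2 and 4 |
| In-person only | 1 and 2 | 3 and 4 |
| Both | 1, 2 and 3 (leaves 4) | 2, 3 and 4 (leaves 1) |

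When neither component shows benefit, the wording leaves only the most intensive condition.

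**Consistency with step 3.** Step 3 takes forward screened-in components only. A screened-out component therefore has its lower level struck by step 2, while its higher level has no written route onward. The two steps do not fit together as worded. With *higher* in place of *lower* they do: the component stays at its lower level, and only screened-in components compete for their higher level.

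**How often the clause would apply.** The only figures in the plan that bear on this are the minimum detectable effects under Sample Size. They reproduce with 32 clusters of 60 parents, SD 1 and two-sided 10% significance:

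- Design effect = 1 + 59 × ICC = 2.18, 3.95 and 6.90 for ICC 0.02, 0.05 and 0.10.
- SE of a main effect = √(4 × design effect / 1920) = 0.0674, 0.0907 and 0.1199.
- Minimum detectable effect at 80% power = (1.645 + 0.842) × SE = 0.168, 0.226 and 0.298.
- At 90% power = (1.645 + 1.282) × SE = 0.197, 0.265 and 0.351.

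The ends of both ranges match the stated values. Now assume that a component is screened in when its estimate is positive with two-sided P<.10. This is the reporting level under Engagement Outcomes in Data Analysis; the selection section states no threshold. By simulation under a normal approximation:

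| True effect (SD) | P(screened in), ICC 0.02 / 0.05 / 0.10 | P(reversed clause applies) |
|---|---|---|
| −0.3 | 0 / 0 / 0 (rounded) | about 1 |
| 0 | about 0.05 at each | about 0.95 |
| +0.3 | 0.997 / 0.951 / 0.805 | 0.003 / 0.049 / 0.195 |

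The clause thus bites most often when the component does nothing or does harm.

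**The case against.** The strongest reply is that this is a slip whose intent is plain. The label of the set, the restriction in step 3 and the resource aim all point one way, and no sentence says that the higher level of a screened-out component goes forward. Figure 3 may state the rule correctly. All of that is fair, and it shows which correction is needed. It does not remove the error, because no text shown states the rule the right way round. Reading the lower level as the worse-performing one does not help either: with no effect there is no worse level, and levels here mean number of sessions or presence of a group.

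Three stronger readings are tempting, and the document does not support them.

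- *The plan selects the higher level whatever the data show, or can only return condition 4.* Step 3 describes screened-in components as showing cost-effectiveness as well as a positive effect, and qualitative findings and posterior expected values also enter. A lower level could still be chosen by those routes.
- *The rule contradicts the sponsor's hypothesis that "the higher dosage of in-person sessions will not be a cost-effective component".* That is a hypothesis about cost-effectiveness still to be tested; the clause is a decision rule triggered by engagement. The two sit awkwardly together but are not contradictory.
- *Screening on averaged main effects is itself an error because the components may interact.* Main-effect screening is the approach the protocol adopts. The interaction is also estimated (Engagement Outcomes, Data Analysis), and nothing bars its use.

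**Conclusion.** The concern holds for the screening step. As worded, step 2 strikes the lower level of a component that showed no benefit, against its own label, step 3 and the stated aim. For a component with no true effect the clause would come into play in about 95% of trials. That figure rests on the assumed P<.10 screen and a normal approximation, and it describes the screening step, not the package finally chosen. No estimate, model or data item is affected. The point still matters because the sentence governs the decision that the trial was set up to inform. Confidence is high that the wording is wrong, and lower on what the team would do in practice, since Figure 3 cannot be seen.

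**What to change.** Replace the sentence with, for example: *A component whose effect on engagement is negative or absent is screened out: its higher level is dropped and the component is set at its lower level.* Check it against Figure 3 and align the two if they differ. Record the correction with a date before the selection results are applied. The Abstract reports that data collection ended in November 2023, so if selection has already been made, the report should say which direction was used. The cost is one sentence, with no new data or model.

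Do not add a requirement that a component keep its higher level only if its effect is also positive with the other component on. Take assumed means of 8, 11, 11 and 11 modules in conditions 1 to 4. Each main effect is ((11 − 8) + (11 − 11))/2 = 1.5, so both components pass, yet each adds 11 − 11 = 0 when the other is present. The requirement would drop both and return condition 1, the worst package at 8 modules. Such contrasts also rest on 8 against 8 clusters, so their minimum detectable effects are √2 times larger: 0.168 × 1.414 = 0.24 to 0.298 × 1.414 = 0.42 at 80% power. If the interaction is to inform the choice, compare the four estimated condition means instead; the planned model already supplies them.
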